**Fig. 1 Fig1:**
[figure not shown]
Flowchart of the DELPHI trial

For subgrouping of the patients according their clinical and histological risk factors and the HPV status of their tumours, both clinical factors as well as HPV results are recorded in electronic case report forms (eCRFs) within the central RadPlanBio platform [30, 31], which is accessible from all participating study centers.

### Treatment description

Patients are being treated at the respective participating center of this trial. Every patient receives a planning CT scan in treatment position for 3-dimensional treatment planning with a clinically approved treatment planning system. All patients receive an individual thermoplastic radiotherapy mask for positioning and will be treated with image-guided, intensity-modulated radiotherapy (IMRT), or alternatively, with intensity-modulated proton therapy. The scar from the neck dissection should be marked by radiopaque material prior to the planning CT scan. IMRT can be performed as static (step&shoot) or rotational irradiation (RapidArc, Volumetric Modulated Arc Therapy).

Contouring of the lymph node regions is being performed according to actual guidelines of the international committees [32, 33].

Two target volumes are defined: planning target volume_adjuvant (PTV_adjuvant) and PTV_boost. Organs of risk to be included and contoured are the spinal cord, brain stem, parotid glands and submandibular glands.

Dose prescription is to a representative point in the target volume, according to ICRU report 78. In addition, the maximal dose in the target volume (Dmax) should not exceed 110% of the prescribed dose in the PTV_boost, and the minimal dose (Dmin) should not be below 95% of the prescribed dose but must be 90% of the prescribed dose at minimum. The volume within the PTV_adjuvant, that receives >2 Gy/fraction, i.e. >110% of the prescribed dose, should be as small as possible.

The target volume doses for all treatment arms and dose de-escalation steps are depicted in Table 2.

**Table 2 Tab2:** Prescribed doses in the study arms

1st dose de-escalation step			
**Treatment arm**	**Number of fractions**	**Dose per fraction**	**Final dose**
High risk	25	1.8 Gy/ 2.2 Gy*	45.0 Gy (adjuvant volume) / 55.0 Gy (boost volume)
	2	2.2 Gy**	59.4 Gy (boost volume)
Intermediate risk	25	1.8 Gy / 2.2 Gy*	45.0 Gy (adjuvant volume) / 55.0 Gy (boost volume)
2nd dose de-escalation step			
**Treatment arm**	**Number of fractions**	**Dose per fraction**	**Final dose**
High risk	22	1.8 Gy/ 2.2 Gy*	39.6 Gy (adjuvant volume) / 48.4 Gy (boost volume)
	3	2.2 Gy**	55.0 Gy (boost volume)
Intermediate risk	22	1.8 Gy / 2.2 Gy*	39.6 Gy (adjuvant volume) /48.4 Gy (boost volume)
Observational study arm^#^			
**Treatment arm**		**Dose per fraction**	**Final dose**
High risk		1.8 - 2.0 Gy	50.0 - 50.4 Gy (adjuvant volume)
		1.8 - 2.2 Gy***	64.0 – 66.0 Gy (boost volume)
Intermediate risk		1.8 - 2.0 Gy	50.0 - 50.4 Gy (adjuvant volume)
		1.8 - 2.2 Gy***	58.0 – 60.0 Gy (boost volume)

*applied as simultaneous integrated boost (SIB); ** applied as sequential boost; ***applied as sequential or simultaneous boost; #In the observational study arm, dose prescription can also performed as per standard operating procedure of the respective centre

For the CTV_boost (irrespective of the treatment arm), the previous tumour region is contoured considering initial imaging performed prior to any treatment (computed tomography, magnetic resonance tomography, positron emission computed tomography), initial pan endoscopy, surgery operation reports and any histopathological reports. In case of lymph node metastases, the respective lymph node level is included in the treatment volume (CTV_boost). The CTV_boost as well as the CTV_adjuvant should be 5 mm below skin at maximum.

The CTV_adjuvant includes the CTV_boost and the elective lymph node regions II to IVa on both sides, and Level Va, Vb and VIIa at the tumour-bearing side and is being further defined as summarised in Table 3. The PTVs are applied using centre-specific margins.

**Table 3 Tab3:** Definition of the adjuvant clinical target volume (CTV)

Definition of the adjuvant CTV:
• The adjuvant volume consists of the CTV_boost and the elective lymph node regions II-IVa (both sides) and level Va, Vb and VIIa of the tumour-bearing side.
**In addition (all study arms):**
• If Level II is affected, level IB will also be included.
• In case of tongue infiltration, level IB will also be included.
• If Level II is affected, the affected side will be included up to the base of the skull (level VIIa and VIIb).
• If the contralateral side is affected, level Va and Vb contralateral will be included.
• If level IVa is affected, level IVb and Vc will also be included.
**In addition for the intermediate-risk arm only:**
• If pN0, neck-dissection of both sides and strict lateral tumour localisation (no infiltration of the ground of the tongue, no infiltration of the uvula (for tumours of the soft palate)) of the tumour of the tonsil, one-sided irradiation of the lymph nodes is performed.
• In case of an ipsilateral lymph node metastasis in level II, neck-dissection of both sides and strict lateral tumour localisation (no infiltration of the ground of the tongue, no infiltration of the uvula (for tumours of the soft palate)) of the tumour of the tonsil, one-sided irradiation of the lymph node levels is performed.
• If Level II is affected, level IB will also be included.

Doses to organs at risk are based on the QUANTEC analysis [5, 34, 35]. The constraints for the maximal dose to the spinal cord (Dmax 45 Gy) and to the brain stem (Dmax 54 Gy) have to be met in all cases. Constraints for the parotid glands should be kept, but only when not compromising the prescribed dose to the CTV. The contralateral parotid gland should receive a median dose below 20 Gy, but in general a median dose as low as possible. 

Irradiation is being performed once daily, 5 times per week. Treatment breaks are not intended and not planned, i.e. treatment breaks have to be compensated after failure of more than 1 fraction at latest. Compensation irradiation can be applied at the weekend or as a second fraction on a day during the week. However, the interval between 2 fractions should be at least 6 h, but favourably 8 h. Not more than 6 fractions per week should be given.

Treatment modifications or discontinuation will be performed at the discretion of the treating physician in cases of unacceptable toxicity, patient request, or medical contraindications, and will be documented accordingly.

### Assessment of toxicities and quality of life

Therapy-related side effects are being scored according to the Common Terminology Criteria for Adverse Events v4.0 (CTCAE 4.0), early and late side effects of the skin are being scored according to the guidelines of the RTOG (Radiation Therapy Oncology Group, http://www.rtog.org/ResearchAssociates/AdverseEventReporting/AcuteRadiationMorbidityScoringCriteria.aspx and http://www.rtog.org/ResearchAssociates/AdverseEventReporting/RTOGEORTCLateRadiationMorbidityScoringSchema.aspx).

Toxicity is scored at study visits before start of radio(chemo)therapy, once per week during radio(chemo)therapy and at the end of radio(chemo)therapy. Thereafter, scoring is performed after 6 weeks, every 3 months within the first 2 years and then every 6 months up to 60 months after end of radio(chemo)therapy. Side effects are being documented as new side effects at their first occurrence, or if an increased grade of a previously recorded side effect has been documented. Furthermore, tumour follow-up care is being scheduled at each of the study visits starting 3 months after end of radio(chemo)therapy at the respective head and neck department. In addition, radiological imaging is being performed regularly after end of therapy.

Patients are being educated regarding the side effects using standardized educational documents for radiotherapy or radiochemotherapy. It is expected, that patients suffer from less side effects in the interventional treatment arms compared to the standard treatment.

All patients of the high-risk arms are receiving simultaneous chemotherapy with cisplatin as per standard protocol, aiming to reach a cumulative cisplatin dose of 200 mg/m^2^ body surface area. Thus, chemotherapy is not being modified within this de-escalation trial.

Serious adverse events are defined according to CTCAE criteria and reported without delay to the study coordination centre. Reporting is performed via eCRFs within the central RadPlanBio platform, which automatically generates notifications to the study coordination centre, including the principal investigator.

In addition to the clinical assessment including outcome and toxicities, patients‘ quality of life is being captured and analysed before start of radio(chemo)therapy, at the end of radio(chemo)therapy as well as at follow-up visits using the QLQ-C30 and the QLQ-HN35 questionnaires of the EORTC in german language.

Patients are actively followed according to the study schedule. Missed visits are documented, and efforts are made to minimise loss to follow-up.

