**Discussion:**

Primary aim of the DELPHI trial is to show that radiation dose reduction is safe and therefore feasible in patients with HPV-positive OPSCC. Secondary objective is to show that radiation-dose reduction leads to less late toxicity compared with standard treatment and thus improves quality of life.

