## Study design

This is a multicentric, non-randomised phase I study, conducted at multiple academic university hospitals in Germany with expertise in head and neck oncology and radiotherapy. It consists of two interventional treatment arms and step-wise dose-reduction depending on risk factors for the development of recurrences. Allocation to the study arms is based on predefined clinical and histopathological risk factors and HPV status, as assessed centrally. Patients are enrolled in the high-risk arm if at least one of the following criteria is met: microscopically residual disease after resection, ECE of one or more lymph node metastases or large tumours (pT4) and a minimum of three lymph node metastases. For the intermediate-risk arm, patients with pT3 tumours or one to three lymph node metastases without any of the risk factors of the high-risk profile are included. Due to the nature of the intervention, blinding of participants and treating physicians is not feasible. The inclusion and exclusion criteria are summarised in Table 1. The schedule of enrolment, interventions and assessments is shown in the Supplementary figure.

**Table 1 Tab1:** Inclusion and exclusion criteria

Inclusion criteria:
• Oropharyngeal squamous cell carcinoma with indication of adjuvant radio(chemo)therapy
• ECOG performance status 0-1
• Experimental arm: HPV16(+) tumours
• Observational arm: HPV16(-) tumours
• Adequate compliance to ensure tumour follow-up care as per study protocol
• Age ≥ 18 years
• Written informed consent
• Neck dissection of at least tumour-bearing side

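### Toxicity scoring is described as scoring of therapy-related side effects, which leaves room for an unblinded attribution judgement to influence the late-toxicity comparison

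*Protocol article*

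**What the plan says.** All of this is in the protocol article.

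- **What is scored** (Assessment of toxicities and quality of life): "Therapy-related side effects are being scored according to the Common Terminology Criteria for Adverse Events v4.0 (CTCAE 4.0". Skin effects are graded by RTOG criteria, and there the qualifier is absent.
- **When** (same section): "Toxicity is scored at study visits before start of radio(chemo)therapy, once per week during radio(chemo)therapy and at the end of radio(chemo)therapy", and then at fixed visits up to 60 months.
- **What is recorded** (same section): "Side effects are being documented as new side effects at their first occurrence, or if an increased grade of a previously recorded side effect has" (cut short here). This rule carries no condition on cause.
- **Blinding** (Study design): "Due to the nature of the intervention, blinding of participants and treating physicians is not feasible". No blinded toxicity assessor is mentioned, and the person who scores is not named.
- **Expectation** (Assessment of toxicities and quality of life): "It is expected, that patients suffer from less side effects in the interventional treatment arms compared to the standard treatment".
- **Objective** (Abstract, Discussion): "Secondary objective is to show that radiation-dose reduction leads to less late toxicity compared with standard treatment and thus improves quality of life".
- **Endpoint** (Endpoints): late toxicity at 24 months by CTCAE 4.0 is a secondary endpoint, named without the therapy-related qualifier.
- **Comparator** (Study design): the non-randomised observational arms. They take HPV-negative patients, heavy smokers whatever their HPV status, and patients enrolled between the two dose steps.

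**The concern.** Every patient has had a resection and a neck dissection on at least the tumour-bearing side, and high-risk patients also receive cisplatin. A swallowing problem, dry mouth, neck stiffness or pain at 24 months can therefore have several causes. The article's only statement of which non-skin events are graded uses the word therapy-related. It does not say whether therapy means radiotherapy, radiochemotherapy or the whole treatment including surgery. If centres take the word as a condition for scoring, somebody has to decide on cause before an event is graded, and treating physicians know whether the dose was reduced.

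At stake is the claim of less late toxicity than with standard treatment. That comparison is already open-label and non-randomised, and arm-dependent attribution would add to any confounding. Events left ungraded for this reason could not be brought back by analysis.

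The word is also hard to square with the pre-treatment visit. Nothing can be related to radio(chemo)therapy before it has started, and deficits left by surgery are what a baseline assessment needs to capture.

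**Working it through.** **Step 1. The texts side by side.** The sentence on scoring carries the qualifier. Three other texts do not: the pre-treatment scoring, the recording rule (first occurrence or higher grade) and the definition of the endpoint. So the article supports two readings. In one, therapy-related is a loose description of the events of interest. In the other, it is an entry condition. No text settles which applies, and centres in a multicentre trial may choose differently.

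**Step 2. The plan's own figures.** The article gives no toxicity rate, effect size or power, so no stated figure bears directly on this point. Its sizing figures reproduce and contain no toxicity input:
- Enrolment: 120 / (1 − 0.06 − 0.15) = 151.9, so 152, as stated.
- Stopping rule (2 of 10, 3 of 20, 3 of 30; exact sequential binomial): the probability of stopping is 0.077 at a 3% recurrence rate and 0.612 at 10%. This agrees with the stated α < 0.1 and 1−β > 0.6.

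**Step 3. What an attribution condition would do.** Let T be the true rate, equal in both groups, and c the share of events attributed to therapy. Then

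recorded rate = T × c, and spurious difference = T × (c_obs − c_int).

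If c_obs = c_int, the difference is zero. The T and c values below are assumptions; none is in the article. The last two columns give the approximate chance of a two-sided p < 0.05 in favour of de-escalation. They use the normal approximation for two proportions: Φ[(d − 1.96·se0)/se1], with d the difference in recorded rates, se0 the pooled and se1 the unpooled standard error. With no bias this chance is nominally 2.5%. The group size of 60 is one risk profile over both dose steps, and 120 is both profiles. An observational group of equal size is assumed.

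| T | c_obs / c_int | Recorded, obs. v de-esc. | Difference (points) | Ratio | 60 v 60 | 120 v 120 |
|---|---|---|---|---|---|---|
| 20–40% | 90% / 90% | equal | 0 | 1.00 | 2.5% | 2.5% |
| 20% | 90% / 80% | 18.0% v 16.0% | 2 | 0.89 | 4.8% | 6.1% |
| 30% | 90% / 80% | 27.0% v 24.0% | 3 | 0.89 | 5.7% | 7.7% |
| 40% | 90% / 80% | 36.0% v 32.0% | 4 | 0.89 | 6.7% | 9.6% |
| 20% | 90% / 70% | 18.0% v 14.0% | 4 | 0.78 | 8.6% | 13.2% |
| 30% | 90% / 70% | 27.0% v 21.0% | 6 | 0.78 | 11.6% | 19.1% |
| 40% | 90% / 70% | 36.0% v 28.0% | 8 | 0.78 | 15.3% | 26.3% |

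Worked line (T = 30%, 90% / 70%, 60 v 60): d = 0.06; se0 = √(0.24 × 0.76 × 2/60) = 0.0780; se1 = √((0.27 × 0.73 + 0.21 × 0.79)/60) = 0.0778; (0.06 − 1.96 × 0.0780)/0.0778 = −1.19; Φ = 0.116.

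Other pairs at T = 30% show that the result simply follows the choice: 95% / 85% gives 3.0 points, 90% / 75% gives 4.5, and 90% / 60% gives 9.0.

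**The case against.** A reader might infer that only events judged therapy-related are graded, and hence that the comparison is biased. The documents do not go that far.

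- **The word only is not there.** The sentence may do no more than name the grading scale. No causality step and no exclusion of unrelated events is described. The baseline scoring, the recording rule and the unqualified endpoint all point to general scoring. This stands, and it makes the defect one of open wording rather than of an established filter.
- **The scorer is not named.** The unblinded parties are participants and treating physicians, and the expected reduction in side effects is the plan's hypothesis, not a recorded belief of assessors. This stands too. Still, no blinded assessor is mentioned, and the treating team would be the usual scorer.
- **The eCRF is not shown.** It may already grade all events and hold a field for relation to therapy. So it cannot be asserted that unattributed findings go ungraded, and the article's silence on procedure is no fault in itself.
- **Bias needs attribution to differ by arm.** The article gives no evidence that it does, and a condition applied equally creates no difference when the true rates are equal.
- **Grading regardless of cause has its own problem.** The observational arms contain HPV-negative patients and heavy smokers. Morbidity from smoking or tumour would enter the comparator and could itself favour de-escalation. This is a fair objection to making the all-cause grade the sole basis of the endpoint. It is no objection to collecting it.
- **The stakes are limited.** Late toxicity is a secondary endpoint in a non-randomised phase I study. The EORTC questionnaires need no physician attribution, although patients are unblinded as well, and they measure quality of life rather than the CTCAE endpoint.

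**Conclusion.** The point holds as a weakness of wording with a possible consequence. Read literally, the stated scoring rule permits an unblinded judgement on cause to decide which events are graded, and it sits awkwardly with the scoring before treatment. If attribution differs by arm in the expected direction, the late-toxicity comparison shifts towards de-escalation.

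That a bias exists, or how large it is, cannot be shown from the article. The 2 to 8 points above rest on assumed true rates of 20 to 40% and assumed attribution of 90% against 80% or 70%. The milder pair raises the chance of a false favourable result only to about 5 to 10%; the stronger pair raises it to about 9 to 26%. These figures illustrate what the wording would allow and are not estimates. The effect is confined to toxicity endpoints. Locoregional control, the recurrence stopping rule and the enrolment figure do not depend on it.

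A correction is worth making because it is cheap and because collection continues: recruitment is expected to run to November 2027 and secondary follow-up to November 2032.

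**What to change.** Replace the scoring sentence with one that says: at every visit, including the one before radio(chemo)therapy, side effects are graded by CTCAE 4.0 regardless of presumed cause, and relation to therapy is recorded in a separate field. The RTOG grading of skin effects can stay as it is.

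Report late toxicity at 24 months in two ways: regardless of cause, with the baseline grade taken into account, and by attribution. Neither is sufficient alone. The first is open to differences between the arms in HPV status and smoking, the second to unblinded judgement. Agreement between them would strengthen the claim, and disagreement would show how much depends on attribution.

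If the eCRF already works this way, only the sentence needs correcting. If it does not, record the date of the change. Patients in the first dose step and many observational patients will have had visits under the old rule, and the analysis should be able to separate the two periods.

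Cost: one sentence, at most one eCRF field, more low-grade entries per visit, and somewhat higher recorded rates in all arms. Treatment and sample size do not change.

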### Endpoints

The primary endpoint of this study is the number of locoregional recurrences. Secondary endpoints include acute toxicities as assessed by CTCAE 4.0, late toxicity 24 months after end of radio(chemo)therapy (CTCAE 4.0), quality of life (assessed prior to, during and up to two years after completion of radio(chemo)therapy), locoregional recurrence rates as well as overall survival after 60 months after end of radio(chemo)therapy.

Outcome assessments are performed according to predefined time points as specified in the study schedule.

### Translational research

Data obtained within this trial should serve for further translational research. Provided patients’ approval, tumour specimen are being collected (as formalin-fixed paraffin-embedded material). If feasible at the respective study center, also blood samples prior to start of radio(chemo)therapy and at the end of the second week of the treatment are being collected, e.g. for evaluation of prognostic markers such as circulating tumour DNA and identification of novel markers or therapeutical targets.

### Statistics

We calculated stopping criteria, i.e. the number of recurrences, for which the trial has to be stopped, considering (interim) analyses after 10, 20 and 30 patients have completed 2-year follow-up. Assumptions are: expected recurrence rate: 0.03 in the de-escalation arms, maximum tolerated recurrence rate: 0.1, probability of stopping the study in error despite the expected recurrence rate is achieved: α < 0.1, probability of correctly stopping the study if the recurrence rate is too high: 1-β > 0.6. The calculated numbers that lead to the study being stopped are: 2 recurrences among the first 10 patients, 3 recurrences among the first 20 patients, 3 recurrences among the first 30 patients. The calculation was performed using the toxbdry function of the clinfun package in R statistics software, which applies a Pocock-type boundary for repeated testing [36–38].

For each of the two interventional arms, 60 patients per risk-profile are necessary (*n* = 120 patients in total), i.e. 30 patients in dose-de-escalation step 1 and 30 patients in dose-de-escalation step 2. After closure of the first dose de-escalation step and before opening of the second dose de-escalation step, patients are being enrolled in the respective observational arm according to their risk profile.

It has been assumed that about 50% of the OPSCC are HPV-driven (defined by p16 overexpression and HPV16 DNA positivity). In addition, it is supposed that 6% of the patients will die before the 24 months follow up has been reached or will withdraw from the study during follow-up. In addition, a dropout rate of 15% is assumed. This leads to 152 patients to be enrolled in the HPV-positive interventional arms. In parallel, about 152 patients will be enrolled in the respective observational arms including drop-outs. The total patient number is thus 304. Additional patients will be enrolled in the observational arm between closure of dose step 1 and opening of dose step 2.

The number of patients in the observational arms is not restricted. The observational arm closes when the interventional arms of the second dose de-escalation step closes.

Missing data will be handled using appropriate statistical methods depending on the type and extent of missingness. Sensitivity analyses may be performed if applicable.

Additional subgroup analyses may be performed for the high-risk and intermediate-risk cohorts.

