**Additional inclusion criteria for intermediate risk arm (at least 1 factor to be fulfilled):**
• pT3R0 and/or
• 1-3 lymph node metastases and no extracapsular spread of lymph node metastasis
Exclusion criteria:
• Cumulative nicotine abuse > 30 packyears for intervention arms. These patients are always included in control arms (regardless of HPV status).
• M1
• R2 resection
• No neck dissection performed
• >7 weeks interval surgery-radiotherapy
• Contraindication for guideline-compliant adjuvant radio(chemo)therapy according to clinical risk constellation
• Malignant tumour disease in the last five years before start of study (except basal cell carcinoma of the skin, in-situ carcinoma of the cervix uteri or breast or tumours with a similar good prognosis that are considered very likely to be cured)
• Any malignant tumour disease in the head and neck region regardless of interval and prognosis
• Previous radiotherapy with potential overlap
• Participation in another clinical trial if, and as result of this, another experimental therapy is necessary or the therapies/study protocols are mutually exclusive (e.g. modified chemotherapy, additional consolidating chemotherapy; immunotherapy). Additional participation in observational studies or supportive therapy studies are allowed
• Any other diseases or conditions that do not allow the patient to assess the nature and scope as well as possible consequences of the clinical study
• Pregnant or breastfeeding women

Dose de-escalation is performed in two steps with a dose-reduction by 10% each. The second dose de-escalation step is opened, when all of the planned 30 patients were accrued to the respective interventional arm, when at least 10 out of 30 patients finished their 24 months follow-up time and if the first stopping criterium (two recurrences within 24 months follow-up among the first 10 patients in the respective interventional arm) has not been reached. Patients enrolled after closure of the de-escalation arms, are being included in the observational arm and receive standard radio(chemo)therapy.

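### The stopping boundaries are evaluated only once 10, 20 and 30 patients have completed two years, with no stated rule for acting at the deciding recurrence and an evaluable set that does not match the wording of the boundary

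*Protocol article*

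**What the plan says.** The Statistics section derives the stopping numbers "considering (interim) analyses after 10, 20 and 30 patients have completed 2-year follow-up". The favourable case is given as "expected recurrence rate: 0.03 in the de-escalation arms". The unfavourable case, against which the arms are to be protected, is "maximum tolerated recurrence rate: 0.1". The error limit in the favourable case is "probability of stopping the study in error despite the expected recurrence rate is achieved: α < 0.1". For the unfavourable case the section asks for "probability of correctly stopping the study if the recurrence rate is too high: 1-β > 0.6". The resulting boundary is "2 recurrences among the first 10 patients, 3 recurrences among the first 20 patients, 3 recurrences among the first 30 patients".

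The Study design section (text after Table 1) uses the first of these numbers as a condition for opening the second dose step. It words the number as "two recurrences within 24 months follow-up among the first 10 patients in the respective interventional arm", and requires that at least 10 of the 30 patients have finished 24 months.

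Four other places bear on the point:
- **Planned timeline:** the 24 months run from the end of radio(chemo)therapy.
- **Assessment of toxicities and quality of life:** tumour follow-up takes place at every study visit from month 3.
- **Statistics, sample size:** on early deaths, "it is supposed that 6% of the patients will die before the 24 months follow up has been reached"; withdrawals during follow-up are placed in the same 6%. With a further 15% dropout this leads to 152 patients enrolled in the interventional arms.
- **Data management and monitoring:** an independent committee reviews safety data regularly and oversees the trial on the basis of the predefined stopping rules.

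**The concern.** Two things do not fit.

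**Timing.** Each boundary is a cumulative count. Once two of the first 10 patients have recurred, waiting for the other eight to reach month 24 cannot change the result. The article nevertheless places the evaluation at completion of follow-up, and it describes no pause in accrual before 30 patients are in the dose step. Patients could therefore start at a reduced dose after the limit for that dose has been met.

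**Who is counted.** The looks are triggered by patients who complete two years, but the counts are worded by order of entry (the first 10, 20 or 30). A patient who recurs and dies at month 15 is among the first 10 but never completes two years. Under a completer count that recurrence is lost. Under an order-of-entry count the trigger cannot be met as written for those 10 patients. These would be the recurrences with the worst outcome, and locoregional recurrence is the primary endpoint.

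**Working it through.** **1. The plan's own figures.** For looks at 10, 20 and 30, the boundary is crossed if there are at least 2 recurrences in the first 10 or at least 3 in the first 30; 3 in the first 20 implies 3 in the first 30. Hence

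P(stop) = 1 − [P(0 of 10)·P(≤2 of 20) + P(1 of 10)·P(≤1 of 20)].

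- Rate 0.03: 1 − [0.7374 × 0.9790 + 0.2281 × 0.8802] = 0.077 (stated: below 0.1).
- Rate 0.10: 1 − [0.3487 × 0.6769 + 0.3874 × 0.3917] = 0.612 (stated: above 0.6).

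By look, the cumulative probabilities are 0.0345, 0.0444 and 0.0773 at 0.03, and 0.2639, 0.3906 and 0.6122 at 0.10. The boundary is correctly calculated. The enrolment figure also reproduces: 120/(1 − 0.06 − 0.15) = 151.9, so 152.

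**2. Delay, without an accrual assumption.** If the deciding recurrence comes before month 12 of that patient's follow-up, and the look waits for that patient's 24 months, the look is more than 12 months later. A deciding recurrence at month 6 means at least 18 months.

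**3. Delay, under assumptions.** The article gives no accrual rate per arm and no recurrence times. Assumed: true 24-month rate 0.10, constant hazard, 30 patients entering uniformly over T months, treatment lasting about 1.25 months, and a recurrence known when it occurs. Results given that the first boundary is crossed (200,000 simulated cohorts per row):

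| T (months) | Mean lead of second recurrence before look 1 (months) | Further patients started in that interval |
|---|---|---|
| 18 | 11.9 | 3.4 |
| 24 | 12.7 | 5.9 |
| 36 | 14.2 | 10.4 |
| 48 | 15.8 | 9.9 |
| 54 | 16.5 | 9.3 |

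Detection at the next three-monthly visit would shorten each lead by up to 3 months. A second simulation used one patient per arm every 1 to 3 months, recurrences confined to months 3 to 24, and whichever look was first crossed. It gave median delays of about 13 to 22 months and about 3 to 10 further patients.

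**4. The 20-patient look.** It falls at about 2T/3 + 24 + 1.25 months. This is later than T, the end of enrolment to the step, whenever T < 75.75 months. In the simulations it followed full enrolment in at least 95% of cohorts.

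**5. Completer count.** Suppose a fraction f of recurrent patients die or leave before month 24 and no others are lost. The rate among completers is then q = p(1 − f)/(1 − pf). With p = 0.10:

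| f (assumed) | q | P(stop) |
|---|---|---|
| 0 | 0.1000 | 0.612 |
| 10% | 0.0909 | 0.547 |
| 25% | 0.0769 | 0.438 |

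If patients without recurrence are also lost, the fall is smaller.

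**6. Event-triggered rule.** Checking after every patient (limit 2 up to patient 10, limit 3 from 11 to 30) gives the same crossing outcomes, hence again 0.077 and 0.612. Extending the count beyond 30 does not. With 152/4 = 38 treated per step, the rate-0.03 figure becomes 1 − [0.7374 × 0.9494 + 0.2281 × 0.7953] = 0.119, above the stated limit of 0.1.

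**The case against.** The strongest reply is that the completion clause describes how the boundary was calculated, while the rule itself is a plain count. The condition for the second step counts recurrences within 24 months among the first 10 patients, and the Endpoints section makes the number of locoregional recurrences the primary endpoint. On that reading a recurrence at month 8 counts whatever follows. The committee reviews regularly and is not barred from acting between looks. How it applies the counts would normally be set out in a charter, which an article need not reproduce.

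Much of this stands. A reader might infer that nobody acts before a look; the article does not say so, and the committee's role leaves earlier action open. A reader might also infer that fatal recurrences are dropped, or that such patients are replaced from the extra enrolment. No sentence says either: exclusion is one reading, and the 152 is an enrolment total without a replacement rule. Nor are the later looks useless. They come too late to limit accrual to their own dose step, but they can still inform the next step and the decision at the end of the trial.

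The delay figures are conditional on crossing the first boundary, which has probability 0.264 at a true 10% and 0.0345 at the expected 3%. The article expects a gap between closing step 1 and opening step 2, which implies T/3 + 25.25 > T, or T below about 38 months. The upper three rows of the delay table therefore fit the plan better than the lower two.

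What does not fall away is the text itself. The article states a trigger, a boundary and a condition for the second step, and the trigger and the counts use different sets of patients. The committee is tied to the predefined rules, and the only timing those rules carry is completion of follow-up. This is a mismatch in what is stated, not an omitted detail.

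**Conclusion.** The point holds in a limited form. The boundary arithmetic is right; the evaluation time and the evaluable set are badly fixed. As written, a boundary already met can wait about a year or more for its scheduled evaluation: about 12 to 16 months on average at the first look, with about 3 to 10 further patients started, under the assumed 10% rate and accrual over 18 to 54 months. The 20-patient look almost always comes after the step is fully enrolled.

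The loss of stopping probability to 0.547 or 0.438 applies only on the completer reading and only for the assumed fractions of 10% and 25%. It shows that the reading matters, because even the smaller fraction takes the design below its stated 0.6. It does not show that the trial is being run that way.

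**What to change.** Reconcile the Statistics and Study design wording in one paragraph, repeated in the committee's charter:

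1. Define the first 10, 20 and 30 patients of each arm and dose step by order of treatment start.
2. Count every locoregional recurrence within 24 months, including those in patients who later die or withdraw.
3. Treat the boundary as reached on the date of the second recurrence among the first 10, or the third among the first 30 treated, whether or not the others have completed 24 months. The limit of 30 must be explicit, because counting 38 would give α = 0.119. What then follows for treatment is for the sponsor and the committee to specify.
4. Keep the 10-, 20- and 30-patient looks as scheduled committee reviews.

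The boundary numbers, α = 0.077, 1-β = 0.612 and the sample size stay as they are. Follow-up visits already take place and outcomes are already collected, so the cost is an amendment of the text and prompt reporting of each recurrence to the committee. Recruitment is expected to run to November 2027, so the change can still take effect.
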